## Abstract

**Background:**

Delirium is a neurobehavioural syndrome that frequently develops in the postoperative setting. The incidence of elderly patients who develop delirium during hospital stay ranges from 10-80%. Delirium was first described more than half a century ago in the cardiac surgery population, where it was already discovered as a state that might be accompanied by serious complications such as prolonged ICU and hospital stay, reduced quality of life and increased mortality. Furthermore, the duration of delirium is associated with worse long-term cognitive function in the general ICU population. This long-term experience with delirium suggests a high socioeconomic burden and has been a focus of many studies. Due to the multifactorial origin of delirium, we have several but no incontestable options for prevention and symptomatic treatment. Overall, delirium represents a high burden not only for patient and family members, but also for the medical care team that aims to prevent postoperative delirium to avoid serious consequences associated with it.

The purpose of this study is to determine whether postoperative delirium can be prevented by the combination of established preventive agents. In addition, measured levels of pre- and postoperative cortisol, neuron specific enolase (NSE) and S-100β will be used to investigate dynamics of these parameters in delirious and non-delirious patients after surgery.

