#### Secondary outcome measures

Incidence of postoperative delirium based on cognitive testing and laboratory parameters:A 1-point drop in Nu-DESC score on 1 of the 3 postoperative daysSignificant elevation of study-specific laboratory values after surgery:○ Elevation of NSE above 16.3 μg/l (normal value)○ Elevation of S-100β above 0.1 μg/l (normal value) or doubling of the preoperative value○ Elevation of cortisol level above 638 nmol/l (upper limit of normal range)

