#### Laboratory assessments of cognitive function

##### NSE

Elevated NSE can be measured in the blood (half-life of roughly 48 h) or the cerebrospinal fluid (half-life of 6–8 h) and is indicative of various pathological conditions. It serves as a marker of acute neuronal lesions as in anoxia, acute brain injury, or inflammatory processes leading to cell destruction. NSE levels are negligible after damage to extracerebral tissue. NSE is quantified in acute brain injury, subarachnoid haemorrhage, stroke, status epilepticus, dementia, active multiple sclerosis, severe central nervous system (CNS) infection, decompensated hypertension, intracerebral and extracerebral neoplasia, cardiopulmonary bypass during heart surgery, cardiac arrest, and neurological metabolic diseases for course documentation and prognostic evaluation.

Although elevated NSE is associated with above-mentioned conditions, Rasmussen et al. identified a significant decrease in NSE after abdominal surgery in a study of 65 patients, but this did not correlate with cognitive dysfunction [22]. Other studies with larger cohorts also showed no difference in NSE levels in delirious and non-delirious patients after investigation of elderly patients who were acutely admitted after hip fracture [23]. However, other data suggest correlation between elevated NSE and delirium in the ICU population [24]. We conclude that the role of NSE in the diagnosis of delirium and its possibility to evaluate long-term outcome is still unclear and needs further investigation.

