##### Cortisol

Serum cortisol levels have been shown to correlate with both the degree of delirium and the risk of developing it, as stress was found to play a major role in delirium and its pathogenesis postoperatively [39]. Serum cortisol has been suggested to be an important marker of risk of postoperative delirium after cardiac surgery in patients with a preoperative diagnosis of major depressive disorder [40].

Serum cortisol levels depend on the patients’ perioperative stress levels. To date, there remains no clear definition of physiological vs. pathological serum cortisol levels following a certain type of surgery. The present study will analyse cognitive decline or present delirium based on the mentioned scores and correlation between serum cortisol levels preoperatively vs. postoperatively.

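### Fixed normal-range cut-offs for NSE, cortisol and (in part) S-100β are counted as delirium incidence without a preoperative reference, at odds with the protocol's own text and aims

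*Protocol article*

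**What the plan says.** The protocol article, under Secondary outcome measures, introduces the list as "Incidence of postoperative delirium based on cognitive testing and laboratory parameters". A parent line requires a significant postoperative elevation of the study's laboratory values, and three rules follow:

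- NSE: "Elevation of NSE above 16.3 μg/l (normal value".
- S-100β: "Elevation of S-100β above 0.1 μg/l (normal value) or doubling of the preoperative value".
- Cortisol: "Elevation of cortisol level above 638 nmol/l (upper limit of normal range".

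Other sections bear on these rules.

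- **Cortisol:** levels depend on perioperative stress, and "To date, there remains no clear definition of physiological vs. pathological serum cortisol levels following a certain type of surgery". The section plans to relate preoperative to postoperative cortisol.
- **NSE:** the conditions in which NSE is measured include "intracerebral and extracerebral neoplasia, cardiopulmonary bypass during heart surgery, cardiac arrest", and the next paragraph says raised NSE goes with the listed conditions.
- **Inclusion criteria:** cardiac surgery is one of six eligible fields; both elective and emergency operations qualify.
- **Interventions:** all three markers are measured before and after surgery.
- **Abstract, Background:** the markers "will be used to investigate dynamics of these parameters in delirious and non-delirious patients after surgery".
- **Secondary analyses:** changes in the three markers are to be quantified.

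**The concern.** A normal-range limit describes people who have not just had an operation. Applied to a postoperative value without regard to the preoperative one, it cannot separate a rise from a level that was already high, and it ignores any rise that stays under the limit. For cortisol, the protocol itself says the postoperative boundary between physiological and pathological is unclear, yet the endpoint sets one boundary for every eligible operation.

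Two comparisons are affected. Between arms, positives unrelated to delirium dilute any treatment contrast. Between delirious and non-delirious patients, nothing is randomised, so type of surgery can influence both marker and delirium and create or hide an association. Counting a laboratory elevation as delirium incidence adds a further difficulty: read literally, the marker helps define the groups across which it is to be compared.

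**Working it through.** The protocol gives no event rate, sensitivity or specificity for any marker endpoint, so there is no figure to reproduce. The check applies the rules as worded; two illustrations on assumed inputs follow.

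**1. What the rules count**

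| Case | Result as worded |
|---|---|
| NSE 18 before, 17 μg/l after | Above 16.3, so can count, although it fell |
| NSE 8 before, 16 μg/l after | Doubled but below 16.3, so does not count |
| Cortisol preoperative 319 nmol/l (638/2) | Can double to 638 without exceeding the limit |
| S-100β preoperative above 0.05 μg/l (0.1/2) | Any doubling already exceeds 0.1, so the doubling clause adds nothing |

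The NSE values are illustrative; the limits are the protocol's. Because the S-100β rule is joined by *or*, the baseline clause can only add positives, namely patients starting at or below 0.05 μg/l. It never removes someone already above 0.1 before surgery. S-100β therefore shares part of the problem.

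**2. Passages side by side**

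- Fixed 638 nmol/l after any eligible operation, against no clear pathological level after a given operation: these conflict.
- Fixed 16.3 μg/l without baseline, against raised NSE in bypass and neoplasia, with cardiac surgery eligible: a positive value can have a source other than delirium.
- Threshold crossing in the outcome list, against dynamics (Abstract), pre/post cortisol (Cortisol) and marker changes (Secondary analyses): two accounts of the marker outcome, with nothing saying which governs.

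**3. Illustration: dilution between arms (assumed inputs)**

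Assume delirium in 35% on placebo (the protocol's 0.35 is an average over arms, borrowed here) and 24.5% on active treatment (30% reduction read as relative: 0.35 × 0.7). Assume every delirious patient is marker-positive, and a fraction f of the others is too.

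- Positive rate = p + f(1 − p), so the arm difference is (1 − f) × 10.5 points.
- Share of placebo positives who are delirious = 0.35 / (0.35 + 0.65f).

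| f | Difference (points) | Delirious share of placebo positives |
|---|---|---|
| 0 | 10.5 | 1.00 |
| 0.1 | 9.45 | 0.84 |
| 0.3 | 7.35 | 0.64 |
| 0.5 | 5.25 | 0.52 |
| 0.7 | 3.15 | 0.43 |

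**4. Illustration: confounding by type of surgery (assumed inputs)**

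Assume 90% of bypass patients and 15% of others exceed the NSE limit, delirium in 50% and 30% respectively, no link within type of surgery, and every cardiac patient on bypass. With 20% cardiac:

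- Cardiac share of positives = 0.2 × 0.9 / (0.18 + 0.8 × 0.15) = 0.60.
- Delirium in positives = 0.6 × 0.5 + 0.4 × 0.3 = 0.42.
- Cardiac share of negatives = 0.02 / (0.02 + 0.68) = 0.029; delirium in negatives ≈ 0.306.
- Pooled odds ratio = (0.42/0.58) / (0.306/0.694) ≈ 1.64.

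The same steps with 10% and 30% cardiac give cardiac shares of 0.40 and 0.72 and odds ratios of about 1.4 and 1.8. These show the direction of the effect and do not estimate its size in this trial.

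**The case against.** The strongest reply is that the plan already looks at change. All markers are sampled preoperatively, Secondary analyses covers changes in all three, and the Cortisol section plans a pre/post analysis. This stands: the missing baseline is a fault of the outcome definitions. A reader might infer that the dynamics aim goes unanswered; the document does not support that. What remains is two unreconciled definitions.

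A reader might also infer that the endpoints will mark the operation rather than delirium. That is too strong.

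- The statement about an unclear pathological level concerns cortisol only and does not extend to NSE.
- The NSE section says damage outside the brain has negligible effect on NSE, and cites a study in which NSE fell after abdominal surgery. The NSE concern is therefore mainly about bypass and tumour patients. In the latter a raised value may precede surgery and so would not mark the operation.
- The Cortisol section reports correlation with the degree and risk of delirium. That justifies studying cortisol but does not validate 638 nmol/l after surgery.

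Other points stand in part. The parent line's wording could be read as requiring a rise, so the NSE 18-to-17 patient is a possible positive, not a certain one; that ambiguity itself needs resolving. Randomisation means unrelated positives dilute the arm contrast without favouring an arm. Patients at high risk of ICU treatment are excluded, with an unclear qualifier, so the cardiac share is unknown. With 200 patients (60 positive, 140 negative), the illustrative odds ratio of 1.64 would have a 95% interval of roughly 0.88 to 3.1, so the trial would often not establish it. Covariate choice is usually left to the analysis plan and its absence here is no fault; it enters only because the outcome rule has to be rewritten.

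**Conclusion.** The point holds in limited form. The NSE and cortisol rules are fixed normal-range limits with no preoperative term, S-100β can be met on its fixed limit alone, and all three are placed under delirium incidence. The cortisol limit conflicts with the Cortisol section, the NSE limit ignores elevation that the NSE section associates with bypass and neoplasia, and all three rules fit poorly with the stated interest in change.

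The consequence is that the endpoints *may partly* reflect type of surgery or pre-existing elevation. That dilutes arm comparisons and can confound the observational marker–delirium comparison. The size cannot be derived from the document; every rate in the two illustrations is assumed, apart from the borrowed 0.35 and 30%. The point concerns secondary outcomes and leaves the primary outcome untouched. It is worth correcting before analysis.

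**What to change.** Reconcile Secondary outcome measures with the Cortisol section and Secondary analyses:

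1. For NSE, S-100β and cortisol alike, make the outcome the log postoperative value adjusted for the log preoperative value, and compare arms on that.
2. Compare delirious with non-delirious patients in the same model, adding surgical field (or cardiac versus non-cardiac if fields are sparse) and elective or emergency status. Define delirium for this purpose without the laboratory values.
3. Keep 16.3 μg/l, 0.1 μg/l or doubling, and 638 nmol/l for descriptive tables only.
4. Do not label a marker elevation as incidence of delirium.

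No new samples are needed. The section on deviations from the analysis plan says analysis starts after recruitment ends and provides for informing the ethics committees and listing changes, so this can be declared beforehand. The cost is the loss of a simple elevated yes/no headline for the markers.

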### Sample size

Sample size was estimated to be able to show the superiority of one treatment arm to placebo by a 30% reduction in the incidence of delirium (efficacy). To achieve power of 0.8, 188 study participants will have to be recruited. To accommodate for drop-out cases the sample size has been increased to 200 (i.e., 50 study participants to be recruited for each treatment arm).

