### Statistical methods

#### Null and alternative hypothesis

The two-sided statistical null hypothesis will test whether the preoperative administration of haloperidol, ketamine or both drugs combined immediately before induction of anaesthesia compared to placebo is unable to prevent the decline of postoperative cognitive function. The alternative hypothesis is that there is an effect of one of the drugs or the combination.

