#### Planned analyses and sample size rationale

##### Primary analysis

Differences among the four groups will be analysed by the chi-square test. Post hoc the groups will be compared by pairwise chi-square test including the Bonferroni correction.

We will follow the intention-to-treat principle. Data on all study participants who have received the study drug as part of one of the four treatment arms will be analysed.

When the sample size in each of the four groups is 50, the 0.05-level chi-square test will have 80% power to detect a difference in proportions characterised by variance (V) of proportions:

V = Σ(π_i_- π_0_)^2^/G of 0.0125 and an average proportion of 0.35

Since study participants will be excluded from the primary analysis if there is a significant decline in MMSE score of at least 2 points during at least 1 of the 3 postoperative days or if they are treated in the ICU after surgery. The determined sample size following power analysis will be increased (see above). This might lead to an uneven number of study participants distributed over the four treatment arms after termination of the study, an occurrence that will need to be taken into consideration.

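### The protocol attaches 80% power to both 188 and 200 participants and to two different targets; by its only fully specified calculation, 200 holds no drop-out reserve

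*Protocol article*

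**What the plan says.** Two sections of the protocol article justify the sample size.

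- *Sample size* (Methods): the aim is to show "superiority of one treatment arm to placebo by a 30% reduction in the incidence of delirium (efficacy"). Then: "To achieve power of 0.8, 188 study participants will have to be recruited". Then: "To accommodate for drop-out cases the sample size has been increased to 200", that is, 50 per arm. No placebo incidence or significance level is given, and the 30% is not called absolute or relative.
- *Primary analysis*: "When the sample size in each of the four groups is 50, the 0.05-level chi-square test will have 80% power", for a variance of proportions V = 0.0125 and an average proportion of 0.35. The four groups are compared by one chi-square test, followed by pairwise chi-square tests with a Bonferroni correction. The number of comparisons is not given.

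*Primary analysis* and *Handling of missing data and drop-outs* also take ICU-treated patients out of the primary analysis. *Primary analysis* points back to the enlarged sample size as the provision for exclusions.

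**The concern.** The same 80% is tied to 188 participants in one section and to 200 in the other. If 200 is what 80% requires, the 12 patients described as a drop-out reserve are part of the requirement, and any drop-out or ICU exclusion takes the trial below its target.

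The two sections also power different questions. A four-group test can reject because two active arms differ, without any arm beating placebo. The objective, repeated in *Primary outcome measure* and in the Discussion, is superiority of an active arm over placebo. That conclusion can come only from the corrected pairwise step, for which no power is stated. With the 30% undefined, a reader cannot tell which effect a null result would speak against.

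**Working it through.** **Inputs.** From *Primary analysis*: level 0.05, V = 0.0125, average proportion p = 0.35, four groups (3 degrees of freedom), 50 per group. From *Sample size*: 188 (47 per arm) before drop-out and 200 after, an implied allowance of 12/200 = 6%.

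**Formula.** Noncentrality λ = N × V / [p(1 − p)], with p(1 − p) = 0.35 × 0.65 = 0.2275. Power is the probability that a noncentral chi-square on 3 df exceeds 7.815.

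**The plan's own figure.** N = 200: λ = 200 × 0.0125/0.2275 = 10.99, power 80.3%. The *Primary analysis* statement reproduces.

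**The other figure.** N = 188: λ = 188 × 0.0125/0.2275 = 10.33, power 77.6%. Rounding of V and p moves this only over 77.1% to 78.1%.

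**N required.** 80% power needs λ = 10.903, so N = 10.903 × 0.2275/0.0125 = 198.4, that is 199, or 200 with equal arms. This is the number analysed. Losing the implied 6% from 200 leaves 200 × 0.94 = 188, hence 77.6%. For scale only: keeping a 6% allowance on top of 200 would mean 200/0.94 = 213 (216 with equal arms).

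**What V describes.** The pattern 50/40/30/20% has mean 35% and V = (0.15² + 0.05² + 0.05² + 0.15²)/4 = 0.05/4 = 0.0125. It is not the only fit. The same mean and V arise from:

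- placebo 54.4% with all active arms at 28.5%;
- one active arm at 15.6% with the others at 41.5%;
- 50.8/35/35/19.2%;
- two arms at 46.2% and two at 23.8%.

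**Arm versus placebo (assumptions, not the plan's figures).** These are simulated Pearson tests with 50 per arm. Success means that the four-group test rejects and at least one active arm beats placebo. Placebo is the first arm, or one of the two high arms in the last pattern.

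| Pattern | 0.05/6 | 0.05/3 |
|---|---|---|
| 50/40/30/20% | 73% | 78% |
| Range over all five patterns | 55–78% | about 63–80% |

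**If 30% is relative.** With an assumed placebo rate of 50% (50% v 35%), pairwise power at 50 per arm is 33% unadjusted and 13% at 0.05/6. Unadjusted 80% power would need 170 per arm.

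**The case against.** **188 may have another source.** *Sample size* gives neither a control rate nor a level. A pairwise comparison of 50% with 20% at two-sided 0.025 needs 47 per arm, which is 188 in total. This stands as a possibility: the documents show a conflict between sections, not a proven slip in computing 188. But that level appears nowhere in the protocol, and a second, unstated basis would still need reconciling with the stated one.

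**The shortfall is small.** This also stands. The formula gives a gap of 2.4 points. Simulation of the planned test under 50/40/30/20% gives 78.9% at 47 per arm and 81.7% at 50, so the shortfall is then about 1 point. Nothing serious rests on that gap alone.

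**The arm-versus-placebo figures depend on choices the protocol does not state.** Correct. Six comparisons is the natural reading of pairwise tests among four groups, while the objective concerns three. Under 50/40/30/20% at 0.05/3, power is 82% if the four-group test is not required to reject first and 78% if it is. For this reason they are given as a range.

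**A tempting stronger reading.** A reader might infer that the 30% reduction is really a fall from 50% to 20%, because 50/40/30/20% fits exactly. The documents give no arm proportions and several other patterns fit equally well, so this is an illustration and not the authors' stated scenario. Nor can it be said that the trial certainly misses 80% for its objective, since the upper end of the range reaches about 80%.

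**Conclusion.** The two sections contradict each other and cannot both stand as written. On the only fully specified calculation, about 199 analysed patients (200 with equal arms) are needed for 80% power on the four-group test, and 188 give about 78%. The figure of 200 therefore includes no allowance for drop-outs or ICU exclusions. This rests on V, the average proportion and the level in *Primary analysis*, and on the noncentral chi-square approximation.

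The stated 80% does not apply to one arm versus placebo. Power for that target is not given. On the assumptions above it runs from 55% to about 80%, depending on the pattern and the number of comparisons. The 30% reduction is undefined. If it were relative from an assumed 50%, the trial would have little power to detect it. The numerical gap between 188 and 200 is minor; the missing reserve and the mismatch of targets are what matter for interpreting the result.

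**What to change.** In *Sample size* and *Primary analysis*:

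1. State one consistent result: for V = 0.0125 and average proportion 0.35, 200 analysed patients give about 80% power and 188 about 78% on the four-group test. If 188 came from another calculation, give its inputs.
2. Withdraw the statement that 200 covers drop-outs, and the reliance on that increase for ICU exclusions.
3. State the arm proportions actually assumed, including the placebo rate, and whether 30% is absolute or relative. These must come from the authors; a pattern worked back from V should not be entered as their assumption.
4. State the number of Bonferroni comparisons and report the power of the corrected arm-versus-placebo comparison under those proportions.

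This needs no additional enrolment and no change to the design; *Trial status* already reports 171 patients recruited by August 2017. The cost is a corrected text with less favourable power figures.

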### Recruitment

All consecutive patients aged 65 years or older scheduled for surgery will be screened for study eligibility and then recruited if consent is given.

### Allocation

#### Sequence generation

The allocation sequence follows computer-generated random numbers provided by the Clinical Trials Center (CTC) Zurich. To reduce predictability of the random sequence, the lists are stored in the office of the head nurse with no access permitted by any member of the study team.

#### Allocation concealment mechanism

Study envelopes containing information on the treatment arm allocated to a specific study participant are assembled by designees who are not member of the study team. For each study participant, two sealed envelopes are prepared: one regular envelope to be handed out to the nurses who prepare the study drug and one emergency envelope to be opened in case of an adverse event. The sealed emergency envelope is stored with the documents detailing the patient’s current and past medical history to guarantee complete access in case of an emergency.

